#### Strand B

Based on a pilot study and the MSIS physical and psychological component scores then a sample size of 22 in each group will be sufficient to show a similar probability (0.217) that an observation after intervention will be less than before intervention as in the pilot study (mean before intervention 23.0, after intervention 18.8). This is based on using the Wilcoxon Signed Rank Test, significance level 0.05 and a power of 90%.

As parametric tests require less subjects for the same power these numbers should be sufficient even if these tests are used instead of the non-parametric tests given above.

### Interventions

The physiotherapy interventions for strands A and B are standardised and based on the latest evidence for practice in order to allow reproduction of the programmes. The Yoga and Fitness Instructor interventions are not specified, in order to represent normal practice, but are well documented to allow comparison later.

To ensure standardisation of physiotherapy interventions, training for those physiotherapists delivering the programmes will be held on three occasions, supporting documentation will be provided and follow up advice and information for deliverers was supplied as necessary by e-mail and telephone. The content of the interventions for both strands is described below. The attendance and participation of each study participant will be documented on a weekly basis.

The control groups in both strands will not receive any intervention for the 12 weeks and were told to continue with their normal routine. Once the control period is over participants will receive the treatment of their choice but the response to this will not be assessed as part of this trial.

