**Methods and design:**

This is a multi-centre, single blind, block randomised, controlled trial. Participants will be recruited via the ten regional offices of MS Ireland. Telephone screening will establish eligibility and stratification according to the mobility section of the Guys Neurological Disability Scale. Once a block of people of the same strand in the same geographical region have given consent, participants will be randomised. Strand A will concern individuals with MS who walk independently or use one stick to walk outside. Participants will be randomised to yoga, physiotherapy led exercise class, fitness instructor led exercise class or to a control group who don't change their exercise habits.

Strand B will concern individuals with MS who walk with bilateral support or a rollator, they may use a wheelchair for longer distance outdoors. Participants will be randomised to 1:1 Physiotherapist led intervention, group intervention led by Physiotherapist, group yoga intervention or a control group who don't change their exercise habits. Participants will be assessed by physiotherapist who is blind to the group allocation at week 1, week 12 (following 10 weeks intervention or control), and at 12 week follow up. The primary outcome measure for both strands is the Multiple Sclerosis Impact Scale. Secondary outcomes are Modified Fatigue Impact Scale, 6 Minute Walk test, and muscle strength measured with hand held dynamometry. Strand B will also use Berg Balance Test and the Modified Ashworth Scale. Confounding variables such as sensation, coordination, proprioception, range of motion and other impairments will be recorded at initial assessment.

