## Methods and design

### Design

This will be a multi-centre, prospective, single blinded, block randomised controlled trial. Participants will be stratified according to mobility level using the mobility section of the Guys Neurological Disability Scale[24]. Those who score 0, 1 or 2 are stratified to stand A, those scoring 3 and 4 to strand B. For each strand blocks of subjects will be randomised to one of the interventions or to the control group.

Strand A will concern individuals with MS who walk independently or use one stick to walk outside. The objective is to compare the immediate and long term effect of yoga, physiotherapy led exercise class, fitness instructor led exercise class to a control group who don't change their exercise habits.

Strand B will concern individuals with MS who walk with bilateral support or a rollator, they may use a wheelchair for longer distance outdoors. The objective is to compare the immediate and long term effect of 1:1 Physiotherapist led intervention, group intervention led by Physiotherapist, or group yoga intervention to a control group who don't change their exercise habits.

The study protocol was approved by 10 regional ethics committees in the Republic of Ireland

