### Assessment

Each participant will be assessed by a blinded assessor who is unaware of group allocation. Assessors will attend training days in order to standardise the measurements.

Assessments will be carried out at baseline (week 1), post-intervention (week 12) and at follow-up (week 24). The following outcome measures will be used for all three assessments: Multiple Sclerosis Impact Scale 29 version 2 (MSIS), Modified Fatigue Impact Scale (MFIS), six minute walk test (6MWT), physiological cost index (PCI), and hand held dynamometry (HHD). In addition the Berg Balance Scale (BBS) and the Modified Ashworth Scale (MAS) will be used for strand B. As equipment for PCI and HHD are not available to all assessors some participants will not have these measures recorded. The more physically demanding outcome measures were separated to avoid fatigue and so the order of testing for strand A was 6MWT including PCI, MSIS, HHD, MFIS. For strand B it was 6MWT including PCI, MSIS, BBS, MFIS, MAS, HHD

A standardised assessment at baseline considered the participants suitability for exercise and measured confounding variables such as level of sensory loss, coordination deficits etc.

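### The plan promises a long-term comparison with control in both strands, but the untreated control period ends at week 12, so no untreated control exists at week 24

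*Protocol article*

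**What the plan says.** Four parts of the protocol article bear on this.

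- **Design (objectives).** For Strand A: "compare the immediate and long term effect of yoga, physiotherapy led exercise class, fitness instructor led exercise class to a control group". For Strand B: "The objective is to compare the immediate and long term effect of 1:1 Physiotherapist led intervention, group intervention led by Physiotherapist"; yoga classes are included likewise, all against control. In both strands the comparator is defined as "a control group who don't change their exercise habits".
- **Assessment.** "Assessments will be carried out at baseline (week 1), post-intervention (week 12) and at follow-up (week 24"), with the same outcome measures at all three visits. No exception is made for controls. The abstract makes none either; it places the later visits at "week 12 (following 10 weeks intervention or control), and at 12 week follow up".
- **Interventions.** "The control groups in both strands will not receive any intervention for the 12 weeks", and then "Once the control period is over participants will receive the treatment of their choice but the response to this will not be assessed".
- **Statistical Analyses.** If variables are reasonably normal, repeated measures ANOVA tests differences between groups and over time. Otherwise, Wilcoxon signed rank tests are used within groups and Mann-Whitney U tests between groups, before and after intervention. There is no rule on control data after week 12.

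**The concern.** The objective needs a control group that still meets its own definition at the long-term visit. The Interventions section removes that group at week 12. An objective stated for both strands therefore cannot be met by the design as described, and no analysis plan can restore a comparator that was never observed.

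If controls are nevertheless measured at week 24 and compared with the intervention arms, a benefit that has lasted could look smaller than it is or be missed. That matters for a trial meant to decide which programme MS Ireland should deliver.

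**Working it through.** **Step 1: the timeline.**

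| Visit | Intervention arms | Control arm |
|---|---|---|
| Week 1 | Baseline | Baseline |
| Week 12 | After 10 weeks of intervention | Untreated: valid comparator |
| Week 24 | 12 weeks after the week 12 visit | Untreated period over; treatment of choice |

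Week 24 is the only assessment after week 12, so it is the only visit that can carry the long-term comparison. The protocol secures no untreated control data at that visit.

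**Step 2: the two possible readings.**

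(a) Controls are not measured at week 24. There is then no comparator, and the Assessment section, which excepts nobody, is contradicted.

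(b) Controls are measured at week 24, as the Assessment section implies. They may by then have had a chosen treatment, so they no longer fit the Design section's definition of control. If they enter the between-group analysis, the week 24 contrast is diluted.

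Neither reading delivers the objective.

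**Step 3: size under reading (b), as an illustration.**

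Inputs from Sample size calculations: Strand A, 60 per group with probability 0.329; Strand B, 22 per group with probability 0.217; significance level 0.05; power 90%. Taking the level as two-sided is my assumption, because the protocol does not say.

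*Reproducing the planned sizes.* Noether's two-sample rank formula is n per group = (z_0.975 + z_0.90)² / [6(p − 0.5)²], with (1.960 + 1.282)² ≈ 10.51.

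- Strand A: 10.51 / (6 × 0.171²) = 59.9, rounded up to 60.
- Strand B: 10.51 / (6 × 0.283²) = 21.9, rounded up to 22.

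Both sizes reproduce, so this formula is used below for a between-group contrast. The protocol names the signed rank test instead. Noether's formula for that test has 3 in place of 6 and gives 120 and 44. That mismatch is a separate matter and the present point does not depend on it.

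*Diluting the contrast.* Assume a normal-shift model in which the intervention arms keep their full effect at week 24 and controls gain a fraction f of it. With Φ the standard normal distribution function, and d = −Φ⁻¹(p):

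- diluted probability: p_f = Φ(−d(1 − f))
- power: Φ(|p_f − 0.5| × √(6n) − 1.96)

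| f | Strand A p_f | Strand A power | Strand B p_f | Strand B power |
|---|---|---|---|---|
| 0 | 0.329 | 90% | 0.217 | 90% |
| 0.25 | 0.370 | 69% | 0.279 | 72% |
| 0.50 | 0.412 | 38% | 0.348 | 42% |
| 0.75 | 0.456 | 13% | 0.422 | 14% |

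For example, Strand A at f = 0.25 gives 0.130 × √360 − 1.96 ≈ 0.51, and Φ(0.51) ≈ 69%. At f = 1 no difference remains to detect.

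**Step 4: when the sign could reverse.** Let E be the effect, r the share that the intervention arms retain at week 24, and f the share that controls have gained. The expected difference is (r − f)E. It turns negative only if r < f, that is, only if the loss in the intervention arms (1 − r) exceeds the controls' shortfall (1 − f). The protocol gives neither r nor f.

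**The case against.** The strongest reply has four parts.

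1. **The response to the chosen treatment is not assessed, so there may be no treated-control data to bias anything.** This stands in part. On that reading the result is an objective that cannot be answered, not a biased estimate. But the sentence says that the response is not assessed, which is not the same as saying that controls are not measured at week 24, and the Assessment section does not except them. A reader might infer outright that controls miss that visit; the text does not settle it.

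2. **The analysis section does not say that week 24 controls enter the ANOVA.** This stands. A reader might infer that the planned model mixes a sound week 12 contrast with an unsound week 24 one. The text says only between groups and over time, and the non-parametric route, worded as before and after intervention, fits weeks 1 and 12 naturally. Which visits enter a model is often left to an analysis plan. What remains is that nothing shown excludes those data, while the Design section calls for a long-term contrast with control.

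3. **The size is hypothetical.** This stands. A reader might take the Strand A pilot change of 62.4 − 53.6 = 8.8 points, suppose that controls gain all of it while intervention arms keep half, and conclude that the week 24 result would be reversed: 4.4 − 8.8 = −4.4. The protocol does not support that as a general result. The 8.8 is a before-after change in a pilot, not an effect against control. Full gain by controls is the extreme case, and the start date and uptake of the chosen treatment are not given.

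4. **Treating controls afterwards is a common trade-off, and week 12 is intact.** Both are true. Offering treatment is not the fault; keeping an objective that it rules out is. Nor does the missing start date rescue the objective, since freedom from intervention is stated for 12 weeks only.

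**Conclusion.** The point holds as a contradiction within the protocol. The long-term comparison with an unchanged control group, stated as an objective in both strands, cannot be delivered, because the control group is untreated only to week 12 and the one later visit is at week 24. This conclusion needs no numerical assumption.

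Any distortion of the week 24 contrast is conditional on controls being measured then and entering the between-group comparison. Its size depends on unknown uptake, timing and effect. The fall in power from about 90% to between 69% and 13% in Strand A (72% and 14% in Strand B), for controls gaining a quarter to three quarters of the effect, rests on the normal-shift model, full retention in the intervention arms and the planned group sizes. It is an illustration, not a forecast.

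The week 12 comparison with control is sound on this point. At week 24, maintenance within the intervention arms and comparison among them both remain possible.

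**What to change.** Reconcile the Design, Assessment, Interventions and Statistical Analyses sections, without altering what controls are offered:

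- State in the objectives of both strands that comparison with control is made at week 12 only.
- Restate the week 24 objective as maintenance from week 12 to week 24 within the intervention arms, and comparison among the three of them.
- Say in the Assessment section whether controls attend at week 24.
- Add to Statistical Analyses that control data after week 12, if collected, stay out of the between-group model and may only be described.

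The cost is some rewording, one added analysis rule and the loss of a long-term claim against control that the design could not support. Sample size and the week 12 analysis do not change on this account.

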#### Strand A

##### Intervention 1 – Physiotherapy led strength and aerobic training

Participants will attend an hour long circuit class once a week for ten weeks. This will be a circuit style class consisting of Sit to stand/squat, bridging, resisted shoulder flexion, walking/bike, resisted elbow flexion, lunges or resisted knee extension, hip extension, calf raises. All exercises will be completed at 50 – 80% of the participants' one-repetition-maximum and the load will be increased by 2 – 5% when twelve repetitions are easily achieved. The aim is for the participant to be failing on the last repetition. If the next available load is higher than 2 – 5% (such as going from 1 kg to 2 kg in resisted shoulder flexion) the participant can increase the repetitions so that they are still failing to achieve full range on motion on the last one. The primary aim is to achieve "overload" of the muscle to achieve gains in strength. Participants will be educated about the overload principle and that delayed onset of muscle soreness is a normal phenomenon. After five weeks of attending the class, participants will be advised to complete a second hour of strengthening themselves at home.

A second component of the class will be advice regarding aerobic exercise. In the first class, 10 minutes will be devoted to formally explaining aerobic exercise, Uhtoff's phenomenon (whereby increasing heat in people with MS can temporarily exacerbate symptoms) and the evidence supporting aerobic activity.

Each participant will be given a target heart rate. This will be calculated using the Karvonen formula which is: Target Heart Rate = Resting Heart Rate + 65% (Maximum Heart Rate).

The participants will be advised in the initial assessment how to get their resting heart rate, by feeling their carotid pulse for 30 seconds first thing on waking. The first beat they feel will be zero. As a maximal exercise test will not be conducted, each participant's age predicted maximum heart rate will be used as the target HR (i.e. 220 – age). If they are unable to detect a pulse they will aim to exercise at a Rate of Perceived Exertion level of 11 – 14.

Participants will be initially asked to complete two sessions of independent aerobic activity per week for twenty – thirty minutes. From week 5, they will be asked complete this three times a week. Participants can choose the type activity that they did (i.e. swimming/walking/running/cycling). They will take their pulse every ten minutes to ensure they are achieving the correct intensity.

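### The printed target heart rate formula omits the subtraction of the resting rate, and a later sentence calls 220 − age the target; as written, both set near-maximal, maximal or unattainable intensity for independent exercise

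*Protocol article*

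**What the plan says.** The relevant text is in the protocol article, Interventions, Strand A, Intervention 1 (physiotherapy-led strength and aerobic training).

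- **Formula.** Everyone in this arm receives an individual target. The article introduces the rule with the words "This will be calculated using the Karvonen formula which is", and the expression that it then prints reads "Target Heart Rate = Resting Heart Rate + 65% (Maximum Heart Rate)". The bracket holds one term only.
- **Resting rate.** Participants obtain it themselves, "by feeling their carotid pulse for 30 seconds first thing on waking".
- **Maximum.** Because there is no maximal exercise test, the "age predicted maximum heart rate will be used as the target HR", given as 220 − age.
- **Fallback.** Those who cannot detect a pulse aim for a perceived exertion of 11 to 14.
- **Use.** "Participants will be initially asked to complete two sessions of independent aerobic activity per week", each of 20 to 30 minutes, rising to three a week from week 5. "They will take their pulse every ten minutes to ensure they are achieving the correct intensity".

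Two other sections bear on how far this matters. Under Interventions, the physiotherapy programmes are described as standardised so that they can be reproduced, and for the physiotherapists delivering them "supporting documentation will be provided and follow up advice and information for deliverers was supplied as necessary". Under Assessment, "A standardised assessment at baseline considered the participants suitability for exercise".

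**The concern.** A training target has to lie between the resting rate and the maximum. The printed formula adds the whole resting rate to 65% of the whole maximum, so the resting part is counted twice and nothing keeps the result below the maximum. The sentence on 220 − age then gives the maximum itself the name of the target. The same section therefore yields two different targets, and neither is a workable training intensity. No other part of the article caps or corrects them.

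The number matters because it is the working control on intensity in sessions done without supervision. A participant who compares a pulse with the printed target would be told to work harder until close to, at or beyond the predicted maximum. The same section warns that a rise in body heat can temporarily worsen MS symptoms. Anyone reproducing the programme from the article would inherit the wrong target.

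**Working it through.** **Inputs**

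- R = resting heart rate. The article gives no values, so 50 to 80 bpm is assumed and shown as a range.
- M = 220 − age, from Strand A, Intervention 1. The lower age limit is 18 (Participants) and no upper limit is stated. Ages 40, 50 and 60 are used as illustrations, with 20 and 70 as wider bounds.
- Intensity 65%, from the printed formula.

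The article gives no worked target, so there is no figure of its own to reproduce.

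**Formulas**

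- Printed: T = R + 0.65M.
- With the resting rate subtracted: T = R + 0.65(M − R) = 0.35R + 0.65M.
- Printed minus corrected: 0.65R.

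**When the printed target passes the maximum**

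R + 0.65M > M gives R > 0.35M.

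- Age 40: 0.35 × 180 = 63 bpm
- Age 50: 0.35 × 170 = 59.5 bpm
- Age 60: 0.35 × 160 = 56 bpm

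**Which form is coherent**

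Replace 65% by 100%. The printed form gives R + M, which lies above the maximum by the whole resting rate. The form with subtraction gives R + (M − R) = M, as full intensity should. This uses only the article's own terms.

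**Printed target, bpm (% of 220 − age)**

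| R (assumed) | Age 40, M = 180 | Age 50, M = 170 | Age 60, M = 160 |
|---|---|---|---|
| 50 | 167.0 (92.8%) | 160.5 (94.4%) | 154.0 (96.3%) |
| 60 | 177.0 (98.3%) | 170.5 (100.3%) | 164.0 (102.5%) |
| 70 | 187.0 (103.9%) | 180.5 (106.2%) | 174.0 (108.8%) |
| 80 | 197.0 (109.4%) | 190.5 (112.1%) | 184.0 (115.0%) |

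Example, age 50 and R = 70: 70 + 0.65 × 170 = 70 + 110.5 = 180.5; 180.5 / 170 = 106.2%.

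At the lowest assumed resting rate, 50 bpm, the target is 50 + 0.65 × 200 = 180 at age 20 (90% of 200) and 50 + 0.65 × 150 = 147.5 at age 70 (98% of 150). It is near-maximal even there.

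**The 220 − age sentence taken literally**

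T = M, which is 100% of predicted maximum at every age (180 bpm at age 40).

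**Corrected target at R = 70**

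- Age 40: 70 + 0.65 × 110 = 141.5 bpm (78.6% of 180)
- Age 50: 70 + 0.65 × 100 = 135.0 bpm (79.4% of 170)
- Age 60: 70 + 0.65 × 90 = 128.5 bpm (80.3% of 160)

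**Excess of printed over corrected (0.65R)**

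32.5 bpm at R = 50, 39 at 60, 45.5 at 70 and 52 at 80, whatever the age.

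**The case against.** The strongest reply is that these are misprints in a condensed article and not the rule that was applied.

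- **The method is named.** The users are physiotherapists who were trained on three occasions and given supporting documentation. That participants received the wrong number is not shown. This stands: the documentation is not available, so the harm is a risk if the printed text is followed.
- **The 220 − age sentence is a one-word slip.** It opens by saying that no maximal test will be done and names the age-predicted maximum, so it evidently supplies M for the formula. This also stands, and makes it the lesser of the two errors. But reading it that way leaves the formula still wrong.
- **The error partly exposes itself.** Someone calculating a target above 220 − age could notice the conflict. That helps least at low resting rates, where the result is 90% to 98% of maximum (at 50 bpm, ages 20 to 70) and does not look impossible.
- **There are safeguards.** These are the baseline check of suitability for exercise, the first-class explanation of aerobic exercise and heat effects, and the weekly physiotherapist-led class. They lower the risk without correcting the number. The perceived-exertion range suggests that maximal effort was not intended, but it applies only to those who cannot feel a pulse.
- **The reach is narrow.** This is one component of one of three active arms in Strand A, and the percentages depend on assumed resting rates. Both are true. The threshold R > 0.35M and the excess of 0.65R need no such assumption.

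**Conclusion.** The point holds: the text is wrong as written. The printed formula exceeds the article's own predicted maximum for any resting rate above 35% of that maximum, and it is too high by 0.65 times the resting rate for everyone. With an assumed resting rate of 70 bpm the target is 104% to 109% of predicted maximum at ages 40 to 60. The companion sentence, read literally, sets 100%. No outside source is needed, because a training target above the stated maximum is impossible on the article's own terms.

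Whether participants were given the printed number is unknown, and so is how many would be affected. The sample size, outcomes and analysis are untouched. It should be fixed because the rule governs the intensity of unsupervised exercise in a programme meant to be reproducible.

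**What to change.** 1. Print the formula as: Target Heart Rate = Resting Heart Rate + 65% × (Maximum Heart Rate − Resting Heart Rate).
2. Reword the later sentence so that 220 − age is used as the maximum heart rate, not the target.
3. Keep perceived exertion 11 to 14 as the fallback when no pulse can be felt.
4. Check that the physiotherapists' supporting documentation carries the corrected rule, and amend it only if it does not.

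Since 0.35R + 0.65M is below M whenever R is below M, the corrected target can never exceed 220 − age. The cost is two phrases in one section and one check of existing material, with no change to design, sample size or analysis.
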